### Data safety and adverse event monitoring and reporting

Adverse events will be monitored for by the clinical investigators and research midwife at ward rounds or perinatal review sessions. The research midwife will also monitor for adverse events as she extracts clinical data from the case notes. Adverse events entered into the data management software will automatically trigger the generation of an email alert to the obstetrician and paediatrician investigators. Additionally, results of the EPDS within the psychosocial questionnaire will be monitored to ascertain offers of referral.

A Data Safety Monitoring Committee (DSMC) has been formed to assess emerging external evidence in relation to STan, and to monitor adverse events, compliance with trial protocol and progress of recruitment. The DSMC will be notified of and meet as soon as possible after the occurrence of any of the following adverse events: maternal death; and fetal or neonatal death that could be reasonably attributed to, or partly caused by, CTG + STan or CTG alone. The DSMC will also be notified of and asked to deliberate on adverse events including unplanned intensive care admissions (maternal or neonatal) and any other adverse event of significant concern to the investigators or clinical staff. The committee will also be convened in the event that the chief investigator (CW) receives a report of an adverse event, due to STan monitoring, from weekly alerts of the published literature. Responses of the DSMC may include cessation of the study or modification of the protocol, which will in turn be re-submitted to the ethics committees.

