### Data collection

Maternal and neonatal data will be collected from retrospective case-note review by the research midwife who is not involved in the primary provision of care. The treatment allocation cannot be concealed because the content of the notes will reveal the care received. An independent review of 20 records will be completed to validate the quality and accuracy of data entry. Outcomes and timepoints of data collection are detailed in Fig. 2. Prospectively collected data will also be obtained in order to construct a CONSORT flow chart [29, 30].

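### Prompt safety-committee review of a fetal or neonatal death depends on an attribution judgement by an unnamed assessor; maternal death carries no such condition

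*Protocol article*

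**What the plan says.** All of the reporting rules are in the protocol article, Data safety and adverse event monitoring and reporting. They form two tiers and a general remit.

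- **Tier 1, notification and a prompt meeting.** The first event listed is unconditional: "The DSMC will be notified of and meet as soon as possible after the occurrence of any of the following adverse events: maternal death". The second is conditional: "fetal or neonatal death that could be reasonably attributed to, or partly caused by, CTG + STan or CTG alone".
- **Tier 2, notification and deliberation.** This covers "unplanned intensive care admissions (maternal or neonatal) and any other adverse event of significant concern to the investigators or clinical staff". No prompt meeting is required.
- **General remit.** The DSMC was formed to follow external evidence on STan and "to monitor adverse events, compliance with trial protocol and progress of recruitment".

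On who sees events first: "Adverse events will be monitored for by the clinical investigators and research midwife at ward rounds or perinatal review sessions". Entries in the data system "automatically trigger the generation of an email alert to the obstetrician and paediatrician investigators". The section does not say who decides whether a death is attributable to the monitoring.

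Under Data collection, on case-note extraction by the research midwife: "The treatment allocation cannot be concealed because the content of the notes will reveal the care received".

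Under Secondary outcomes, intrapartum fetal death and neonatal death are both listed with no attribution condition. Statistical analysis specifies intention to treat by randomised allocation and says that the trial is underpowered to determine equivalence of neonatal outcomes.

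**The concern.** The trial hopes to lower emergency caesareans from 17% to 12% by reducing false-positive diagnoses of fetal distress, in women selected because their babies are at raised risk. The mirror-image harm is a compromised baby who is not recognised in time. Such a failure to act is hard to pin on a monitor in a single case. An excess of deaths in one arm shows only when all deaths are counted by arm.

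The notification rule works the other way: it asks for a causal verdict before the committee must hear of the death. In an open-label trial that verdict may be reached with the arm known, and could lean differently in the two arms without any bad faith. The DSMC can recommend stopping the trial or changing the protocol, so the information it receives should not be screened beforehand. The rule gives no reason for treating the baby's death differently from the mother's.

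**Working it through.** **1. Which route does each kind of death take?** The plan states no figure for this rule, so the check begins with its wording.

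| Event | Tier 1 (prompt meeting) | Intensive care route | Discretionary route | General remit |
|---|---|---|---|---|
| Maternal death | Always | Not needed | Not needed | Yes |
| Neonatal death after unplanned intensive care admission | If judged attributable | Yes, for the admission | If staff are concerned | Yes, content not stated |
| Neonatal death before any such admission | If judged attributable | No | If staff are concerned | Yes, content not stated |
| Fetal death | If judged attributable | No | If staff are concerned | Yes, content not stated |

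For the last two rows, every specified route passes through someone's judgement: attribution in tier 1, or the wording "any other adverse event of significant concern to the investigators or clinical staff" in tier 2. Even in the second row the unconditional notification is of the admission, and it carries no duty to meet promptly.

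**2. Can the judgement differ by arm?** Allocation is visible in the case notes, and the midwife who extracts them also looks for adverse events. The clinical investigators who look for events work on the wards of an open-label trial. Alerts go to obstetrician and paediatrician investigators, who presumably know the arm or can find it. The text provides no masked assessor.

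**3. How many deaths are involved?** The input from the documents is 1818 randomised, 1:1, so 1818 / 2 = 909 expected per arm. The death rate is an assumption, since the documents give none. With equal arms:

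- 1 per 1000: 1818 × 0.001 = 1.8 deaths
- 2 per 1000: 1818 × 0.002 = 3.6 deaths
- 3 per 1000: 1818 × 0.003 = 5.5 deaths
- wider range, 0.5 to 5 per 1000: 0.9 to 9.1 deaths

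**4. What could an attribution filter hide?** This is an illustration with assumed inputs. Let r be the CTG-arm death rate, suppose a true doubling in the STan arm, and let q be the share of deaths judged attributable, the same in both arms. The counts passing the filter are independent Poisson variables with means 909 × 2r × q (STan) and 909 × r × q (CTG). At r = 0.002 and q = 1 these are 3.64 and 1.82. The table gives the probability that the STan count exceeds the CTG count by three or more.

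| r | q = 1 | q = 0.5 | q = 0.25 |
|---|---|---|---|
| 1 per 1000 | 0.16 | 0.05 | 0.01 |
| 2 per 1000 | 0.37 | 0.16 | 0.05 |
| 3 per 1000 | 0.52 | 0.27 | 0.10 |
| 5 per 1000 | 0.71 | 0.46 | 0.22 |

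These figures treat a death judged unattributable as never reaching the DSMC by another route, so they bound the effect from above. They include no difference between arms in q, which would be an additional distortion.

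**The case against.** The case for leaving the rule alone has several good parts.

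- **Deaths can arrive by other routes.** A reader might infer that an unattributed death never reaches the DSMC. The text does not say so. Unplanned neonatal intensive care admissions are notified with no causal test, many neonatal deaths would plausibly follow such an admission, and there is a discretionary category and a general remit. This stands, except for fetal deaths and deaths before admission.
- **Nobody is said to judge unmasked.** It is tempting to state that unblinded staff decide attribution. The article names no assessor, and its remark on concealment concerns case-note extraction. The visible arm is a reasonable inference, not a stated fact, and nothing shows that attribution would in practice differ by arm.
- **The trial's comparison of deaths is not filtered.** A reader might conclude that an imbalance in deaths could vanish from the results. It could not, because both death outcomes are secondary outcomes analysed by intention to treat. This stands fully.
- **The threshold is permissive.** Possible or partial causation is enough, and either monitoring method qualifies. This makes a low q less likely but does not remove the judgement.
- **Every labour is reviewed.** A multidisciplinary panel looks at all labours and deliveries within 6 weeks of birth. Its stated task is adherence to monitoring protocols, with feedback to providers. No link to the DSMC is described.
- **Deaths will be too few for a test.** Five deaths all in one arm give a two-sided exact binomial p of 2 × (1/2)^5 = 0.0625. This is true, and case review therefore matters. But it argues for sending the committee every case, not fewer.

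The absence of by-arm safety tables is not part of this point. A committee charter may supply them and is not shown.

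**Conclusion.** The point holds for interim safety review and no further. The article fixes a rule under which prompt DSMC attention to a fetal or neonatal death turns on an attribution judgement, while a maternal death has no such test. For fetal deaths and deaths before intensive care admission, the remaining routes are discretionary or unspecified. The final analysis and the sample size are untouched.

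The size cannot be fixed from the documents, because both the death rate and the share judged attributable are assumed. At 1 to 3 deaths per 1000 the whole trial expects about 2 to 5. If half were screened out and arrived by no other route, the chance of the committee seeing an excess of three or more under a true doubling would fall by roughly half or more (0.52 to 0.27 at 3 per 1000; 0.16 to 0.05 at 1 per 1000). The conclusion does not depend on those figures. It rests on the wording of the rule, the visible allocation and the harm that the intervention could plausibly cause. It is a weakness of design that should be corrected, not a contradiction in the text.

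**What to change.** In the tier 1 rule, end the wording "fetal or neonatal death that could be reasonably attributed to, or partly caused by, CTG + STan or CTG alone" after the word death, so that every fetal and neonatal death after randomisation is notified to the DSMC with its arm, on the same footing as maternal death. Leave the question of attribution to the committee.

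The cost is a change of wording in the protocol, and in the committee's charter if it repeats the rule, together with the usual ethics notification. In use it means a few extra notifications and possibly extra meetings: about 2 to 5 deaths in total at the assumed 1 to 3 per 1000, some of which would have been notified anyway. The article reports recruitment as still open, so the change could take effect during the trial. No analysis or sample size figure changes.

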### Dissemination of results

Results will be disseminated via peer-reviewed publications as well as at institutional and state-based clinical meetings and national and international conferences such as the Perinatal Society of Australia and New Zealand and the Royal College of Obstetrics and Gynaecology. It is expected that the study will also be the subject of journal clubs and Twitter feeds, and we will ensure that the results are translated into relevant clinical guidelines, practice and policy briefs, news releases, educational sessions and one-to-one briefings. Results will also be directly disseminated via the Women’s Healthcare Australasia Clinical Network.

## Discussion

About 20% of Australian babies are delivered via emergency caesarean section [8]. At 35% overall, Australian caesarean section rates continue to remain above the OECD average (34% in 2014) and are among the highest in the world, ranking 24th out of 31 OECD countries (rates ranked lowest to highest) [40]. This will be the first Australian trial to examine the potential for STan technology to reduce this rate. It will also be among the first to consider a more comprehensive examination of STan, taking into account both the impact on broader psychosocial well-being and patient preference, as well as cost-effectiveness. Professional bodies such as the Royal Australian and New Zealand College of Obstetrics and Gynaecology are currently relying on international evidence which our critique demonstrates is not generalisable to Australian practice.

In previous trials, very little attention has been paid to the views of women, midwives and obstetricians. This may partly explain the problems experienced with uptake in some settings [41]. In order to identify associated psychosocial and organisational issues, we have already conducted qualitative research with women throughout the hospital [37] as well as obtaining the views of midwives and obstetricians about the introduction of STan and the accompanying educational programme [42]. In-depth, semi-structured interviews incorporating hypothetical written scenarios of STan and CTG revealed that women’s views about monitoring are multifaceted and likely to be influenced by perceptions related to four key factors: risk in labour; mobility in labour; autonomy and choice in labour; and trust in maternity providers [37]. In contrast, doctors and midwives indicated four important areas for consideration when introducing STan: a philosophy of care; the implementation process (including training and education); the existence of research evidence; and attitudes towards new technology [42].

This research will provide Australian evidence for clinical practice and guideline development which is crucial for policy-makers and consumers to make informed, evidence-based choices about care in labour. Given the ubiquitous application of CTG monitoring, we also anticipate that the trial will initiate and inform professional discussions about monitoring at an international level.

### Trial status

The trial is currently recruiting participants. Current protocol version 28 (13 March 2019). Recruitment commenced in 22 January 2018; expected recruitment completion is July 2020. The primary investigator will notify the trial register, the ethics committees, the DSMC and this journal should any major changes be made to the trial protocol.

## Data Availability

Not applicable.

## Abbreviations

AHTA: Adelaide Health Technology Assessment
CI: Confidence interval
CONSORT: Consolidated Standards of Reporting Trials
CTG: Cardiotocography
DCE: Discrete Choice Experiment
DSMC: Data Safety Monitoring Committee
EPDS: Edinburgh Postnatal Depression Scale
FSEP: Fetal Surveillance Education Program
MNL: Multinomial logit
NHMRC: National Health and Medical Research Council
OECD: Organisation for Economic Co-operation and Development
OR: Odds ratio
RANZCOG: Royal Australasian and New Zealand College of Obstetrics and Gynaecology
RR: Risk ratio
STan: ST analysis
START: STan Australian Randomised controlled Trial
